### Sample size calculation

We have based our sample size calculation on our pilot study data (*N* = 53), where the primary outcome event rate (incidence of FAI) is 40% for the sport specialists at the MVPA level (group 1) and 15% for the non-sport specialists at all physical activity levels (group 2). These proportions very closely match prior cross-sectional research that evaluated the incidence of FAI among athletes [10]. Because we have looked at early data from the pilot study to inform our calculation, we have adjusted our type I error rate. To achieve 80% power for a two-sided test at alpha = 0.01, we will require a sample size of 81 in each exposure group (Table 4). Given that some participants’ activity levels may change during the course of the study (where they may change from sport specialist to non-specialist, or vice versa), we will increase the sample size by 10% to ensure we have at least 81 participants in each exposure group. We will also account for a 5% rate of ineligibility (due to a mature hip [closed physes] found on the baseline MRI) and a 10% loss to follow-up rate. Therefore, we require a total sample size of 200 participants. The pilot participants will be rolled into the definitive study.

**Table 4 Tab4:** Per group sample sizes. 80% power, alpha = 0.01, 2-sided testing

	FAI risk in non-sports specialists		
	5%	15%	25%

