### Statistical plan

#### Primary analysis

As previously described, study groups will be defined at the completion of follow-up given participant activity levels may change over time. The proportion of subjects developing FAI in the sport specialist group versus non-sport specialist group will be compared using a logistic regression analysis with FAI as the dependent variable and will include the following independent variables: activity level (sport specialist versus non-sport specialist), body mass index (BMI), and sex. Results will be reported as odds ratios (OR) with 95% confidence intervals and associated *p*-values.

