#### Secondary analyses

We will perform independent samples t-tests to test for differences in 24-month HOS and PedsQL scores between participants who do and do not develop FAI within the 24-month follow-up period. These analyses will be repeated comparing participants who do and do not develop symptomatic FAI. Each secondary outcome will be quantified using descriptive statistics and 95% confidence intervals. We will use multiple imputation to handle missing data.

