#### Subgroup/sensitivity analyses

To assess whether the magnitude of the effect of sport activity on the development of FAI is significantly different in males than in females, we will add an interaction term between sex and sport specialist versus non-sport specialist to the primary logistic regression model. We hypothesize that sport specialization will be more strongly associated with incidence of FAI in males than in females.

No interim analyses are planned. All tests will be 2-sided with α = 0.01. We will use SAS 9.4 (Cary, NC) to perform all analyses.

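### The primary odds ratio is tested at two-sided 0.01 but reported with a 95% interval, so a result with p between 0.01 and 0.05 would show an interval excluding 1 beside a non-significant test

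*Protocol article*

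**What the plan says.** Four statements in the protocol article bear on this point.

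- **Sample size calculation**, on the reason for the strict level: "Because we have looked at early data from the pilot study to inform our calculation, we have adjusted our type I error rate". The study is then sized at that level: "To achieve 80% power for a two-sided test at alpha = 0.01, we will require a sample size of 81 in each exposure group". The same section says that the pilot participants are carried into the main study.
- **Subgroup/sensitivity analyses**, on the level for all testing: "All tests will be 2-sided with α = 0.01".
- **Primary analysis**, on reporting: "Results will be reported as odds ratios (OR) with 95% confidence intervals". The sentence goes on to say that p-values are given as well.
- **Secondary analyses**: "Each secondary outcome will be quantified using descriptive statistics and 95% confidence intervals". The t-tests described in that section fall under the general 0.01 rule.

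The article does not mention a 99% interval, explain why the two levels differ, or call the 95% interval for the primary odds ratio descriptive.

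**The concern.** For the usual Wald analysis, a two-sided test at level α rejects an odds ratio of 1 exactly when the 100(1 − α)% interval excludes 1. At α = 0.01 that is the 99% interval. The 95% interval answers a 0.05 test, so the two statements about the primary result can point in different directions.

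This matters more here than in a study with a conventional alpha. The 0.01 level is the article's stated response to having looked at pilot data, and those pilot participants also count in the final analysis. If the primary p-value came out at 0.02, the printed interval would exclude 1 and the p-value would be below the customary 0.05, while the study's own rule would say not significant. A reader relying on the interval would lose the protection that the lower alpha was meant to give. Choosing the interval level after seeing such a p-value would look selective, so it should be settled beforehand.

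**Working it through.** **Inputs.** From Sample size calculation: FAI in 40% of sport specialists and 15% of non-specialists, two-sided alpha 0.01, 80% power, 81 per group. From Table 4: 30% versus 15% is one of the sponsor's own scenarios (193 per group). Critical values: z = 1.960 for 95%, z = 2.576 for 99%. The calculations are unadjusted for BMI and sex.

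**1. The plan's own figure.** Two-proportion formula with pooled variance under the null: mean proportion 0.275, difference 0.25.

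n′ = [2.576 × √(2 × 0.275 × 0.725) + 0.842 × √(0.40 × 0.60 + 0.15 × 0.85)]² / 0.25² ≈ 73.05, i.e. 74.

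With the continuity correction, n = (n′/4) × [1 + √(1 + 4/(n′ × 0.25))]² ≈ 80.9, i.e. **81 per group**, as stated. The same formula gives all 12 cells of Table 4. The sample size therefore really is built on 0.01, and the mismatch lies only in the reported interval.

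**2. The two intervals at the planned effect, 81 per group.**

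- OR = (0.40/0.60)/(0.15/0.85) = 3.78; log OR = 1.329
- SE = √(1/32.4 + 1/48.6 + 1/12.15 + 1/68.85) = 0.385
- 95% CI: exp(1.329 ± 1.960 × 0.385) = 1.78 to 8.04
- 99% CI: exp(1.329 ± 2.576 × 0.385) = 1.40 to 10.2
- Ratio of widths on the log scale: 2.576/1.960 = 1.31

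Both intervals exclude 1, so a result exactly at the planned effect causes no conflict.

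**3. A result that does conflict.** Take 26/81 versus 13/81 (32% versus 16%).

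- OR = (26/55)/(13/68) = 2.47; SE = √(1/26 + 1/55 + 1/13 + 1/68) = 0.385; z = 0.905/0.385 = 2.35; p = 0.019
- 95% CI 1.16 to 5.26, which excludes 1
- 99% CI 0.92 to 6.67, which includes 1

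With an SE of 0.385, observed odds ratios between about exp(1.960 × 0.385) = 2.13 and exp(2.576 × 0.385) = 2.70 fall in this zone.

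**4. Chance of a split result.** This is the probability that 0.01 < p < 0.05, i.e. power at 0.05 minus power at 0.01.

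| True rates | Wald log-OR | Two-proportion test, no continuity correction |
|---|---|---|
| No effect | 0.05 − 0.01 = 4% (nominal) | 4% (nominal) |
| 40% vs 15% | z = 3.45: 93.2% − 80.9% = 12% | 95.3% − 84.8% = 10% |
| 30% vs 15% | z = 0.887/0.394 = 2.25: about 24% | 63.0% − 38.4% = 25% |

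With the same Wald method the conflict runs one way only: the 95% interval can exclude 1 while the 0.01 test fails, never the reverse.

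**The case against.** The strongest reply is that the decision rule is not in doubt. Every test is at 0.01, the study is sized for it, p-values are printed next to the intervals, and nothing in the article says that significance is judged by whether an interval excludes 1. A confidence level may differ from a test level without making either invalid. A 95% interval labelled as such claims only 95% coverage, and a Wald 99% interval can be recovered from it. All of this stands.

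Several stronger readings therefore fail:

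- A reader might infer that the plan restores a 5% type I error rate. It does not. The error rate belongs to the rule p < 0.01, which is unchanged; only someone who substitutes the interval for that rule would be working at 5%.
- A reader might infer that precision is overstated. The interval is honestly labelled, so this does not follow.
- A reader might infer that every reported result is affected. No interval is stated for the sex interaction. For the secondary outcomes, the sentence places the intervals with descriptive statistics and does not say whether they describe group values or between-group differences. For group values there would be no null value to exclude and no conflict.

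The percentages above are also not chances of a wrong conclusion, because the protocol's answer in that zone is fixed as not significant. They are chances that the printed interval suggests a different answer.

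What the reply does not remove is that the article itself fixes both levels for the primary odds ratio. This is a stated mismatch and not detail left to an analysis plan; a plan that follows the article would carry it forward.

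**Conclusion.** The point holds for the primary odds ratio as a moderate inconsistency between the reported interval and the decision rule. It is not an error in the test, the alpha, the model or the sample size. The nominal chance of a visibly conflicting primary result is 4% under no effect, 10–12% at the planned effect, and about one in four if the specialist rate is 30% instead of 40%. It extends to the secondary outcomes only where a between-group difference is tested at 0.01 and shown with an interval.

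The figures assume 81 per group, large-sample approximations and no covariates. Groups are defined at the end of follow-up, so their final sizes may differ. Adjustment for BMI and sex would shift the numbers slightly. Neither removes the mismatch.

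**What to change.** In Primary analysis, report the 99% confidence interval for the primary odds ratio. In Secondary analyses, do the same for any between-group difference tested at 0.01, and say whether the intervals there are for differences or for group values. If 95% intervals are also shown, label them descriptive and state that conclusions rest on p < 0.01.

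The change is a line or two of text, to be made before the outcome data are analysed. It needs no extra data or participants. The cost is that reported intervals are about 31% wider on the log scale, for example 1.40 to 10.2 in place of 1.78 to 8.04 at the planned effect.

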#### Secondary analyses

We will perform independent samples t-tests to test for differences in 24-month HOS and PedsQL scores between participants who do and do not develop FAI within the 24-month follow-up period. These analyses will be repeated comparing participants who do and do not develop symptomatic FAI. Each secondary outcome will be quantified using descriptive statistics and 95% confidence intervals. We will use multiple imputation to handle missing data.

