### Study objectives

The primary research objective is to determine if sport specialization at the moderate-to-vigorous physical activity (MVPA) level [23–27] is associated with the development of both symptomatic and asymptomatic FAI (i.e. cam, pincer, or mixed-type) in adolescents (ages of 12–14 years) at 2 years post-enrollment determined via MRI.

The secondary research objectives are to determine if the presence of FAI is associated with changes in hip function and health-related quality of life (HRQL) at 2 years post-enrollment determined via the Hip Outcome Score (HOS) and Pediatric Quality of Life (PedsQL) questionnaires.

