#### Secondary outcomes

Secondary outcomes include: 1) hip function and 2) HRQL between subjects with and without any type of FAI at 2 years, as determined by the HOS and PedsQL questionnaires [42, 43].

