#### Outcome measures

Participants will complete the study questionnaires and undergo a physical examination (at baseline and 6, 12, 18, and 24 months) and MRI (at baseline and 24 months) of their dominant hip. Participants will sync their activity tracker data and send their activity log (at baseline and every 3 months until final follow-up at 2 years) (Table 3).

**Table 3 Tab3:** Schedule of events for the PREVIEW study

Data collection	Enrollment	3 M	6 M	9 M	12 M	15 M	18 M	21 M	24 M
Screening and informed consent	●								
Enrolment data (Demographics)	●								
Physical hip examination	●		●		●		●		●
MRI	●								●
Follow-up form	●		●		●		●		●
Activity tracker wear & synchronization	*	x	x	x	x	x	x	x	x
Activity log	*	x	x	x	x	x	x	x	x
Hip Outcome Score (HOS)	●		●		●		●		●
Pediatric QoL Inventory (PedsQL)	●		●		●		●		●
Adverse events			●		●		●		●

*M* months, *MRI* Magnetic Resonance Imaging, * = 1-week post-enrollment/baseline visit, x = 1-week prior to visit

The physical examination will include range of motion (ROM) measurements in all planes documented in the supine and prone positions by a blinded research assistant (using a goniometer), as well as response of provocative hip tests on both hips [44]. Symptomatic FAI in adolescents is typically characterized by anterior hip pain aggravated by flexion activities, decreased hip internal rotation, and a positive impingement sign [7]. We will define symptomatic FAI using the following criteria: 1) positive impingement with groin pain based on flexion, adduction, and internal rotation (FADIR) test, and 2) decreased ROM: internal rotation of the hip when compared to the contralateral side by 5 degrees [45, 46].

We will use a non-contrast three dimensional (3D)-volumetric interpolated breath-hold examination (VIBE) sequence MRI [47]. This protocol has been used to document FAI-related morphology and eliminates the use of intra-articular contrast injections. All MRI and physical examination information will be provided to an independent radiologist adjudicator to determine the incidence of cam, pincer, or mixed-type FAI according to the pre-specified criteria (Table 2). We will also document the change in cartilage volume, labral pathology, herniation pits on the femoral neck, and the extent of physeal closure as these variables may predict future hip osteoarthritis [44].

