## Discussion

The rationale for the PREVIEW study includes: 1) The number and diagnoses of FAI has recently risen and is especially notable within the adolescent populations; 2) High impact and high intensity activity common in many sports have the potential to cause hip damage, especially during physeal closure in the young; 3) There is an increasing trend toward year-round participation in youth sports with early specialization; and 4) An uncertainty regarding “how much is too much” of the same sport activity.

The PREVIEW study is one of the largest prospective cohort studies using MRI to determine the relationship between FAI development during skeletal maturation and physical activity. The eligibility criteria and follow-up period will help to ensure we evaluate the effect of sport activity during the critical phase of hip development and maturation. The sample size calculation is based on actual pilot data to ensure statistical power to detect differences in the incidence of FAI, hip function and HRQL among groups. Outcome assessment bias will be minimized by the use of an objective assessment tool for physical activity as well as independent adjudication of the primary outcome. The feasibility of the study has been demonstrated by the successful completion of the pilot study enrollment.

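### HOS and PedsQL are compared by FAI status with unadjusted t-tests although baseline scores, sex and BMI are to hand, and the Discussion claims power for them that the article's only calculation does not cover

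*Protocol article*

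**What the plan says.** Study objectives sets the secondary question as whether "the presence of FAI is associated with changes in hip function and health-related quality of life (HRQL"), at 2 years after enrolment. Secondary outcomes words it differently, as hip function and "HRQL between subjects with and without any type of FAI at 2 years", and the Abstract does the same. Secondary analyses then fixes the method: "independent samples t-tests to test for differences in 24-month HOS and PedsQL scores". It adds: "These analyses will be repeated comparing participants who do and do not develop symptomatic FAI". No baseline score or covariate enters either set of tests.

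Outcome measures and Table 3 collect both questionnaires at baseline and every 6 months to 24 months. The primary logistic model, by contrast, includes "activity level (sport specialist versus non-sport specialist), body mass index (BMI), and sex".

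The Sample size calculation section and Table 4 use only FAI proportions in the two exposure groups. The Discussion nevertheless says that the calculation rests on pilot data "to ensure statistical power to detect differences in the incidence of FAI, hip function and HRQL among groups".

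**The concern.** There are two separable problems, both in text that the article states rather than leaves out.

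First, FAI versus no FAI is an observed contrast. The study's own hypothesis ties FAI to sport specialisation, and sport participation could plausibly affect hip function and quality of life by other routes. Sex and BMI are judged worth adjusting for in the primary model. An unadjusted difference in 24-month scores therefore mixes any association with FAI with differences in sport group, sex, BMI and starting score. If the objective is about change, the test also leaves out the measurement needed to speak to it.

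Second, a reader who meets a null HOS or PedsQL result alongside the Discussion's assurance of power could take it as an adequately powered negative.

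**Working it through.** **1. The stated sample size.** Inputs from Sample size calculation: 40% vs 15%, 80% power, two-sided alpha 0.01. The mean proportion is 0.275, z(0.995) = 2.576 and z(0.80) = 0.842.

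n = [2.576 × √(2 × 0.275 × 0.725) + 0.842 × √(0.40 × 0.60 + 0.15 × 0.85)]² / 0.25² = 73.05.

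With continuity correction: (73.05/4) × [1 + √(1 + 4/(73.05 × 0.25))]² = 80.9, so 81 per group, as stated. The same formula reproduces all 12 cells of Table 4. No HOS or PedsQL quantity enters it, and the article gives no SD, target difference or correlation for either score.

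**2. Size of the contrast tested.** The secondary tests split by FAI status, not by exposure group. Of 200 participants, the stated 5% ineligibility and 10% loss leave 200 × 0.95 × 0.90 = 171. The 10% allowance for switching exposure group removes nobody from this comparison. With equal exposure groups of 85.5:
- FAI: 85.5 × 0.40 + 85.5 × 0.15 = 34.2 + 12.8 = 47.0
- No FAI: 171 − 47.0 = 124.0

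If only the 162 required (2 × 81) are evaluable, the split is 44.6 vs 117.4.

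**3. How closely FAI is tied to sport group.** Specialists make up 34.2/47.0 = 73% of those with FAI and 51.3/124.0 = 41% of those without. The correlation between FAI and sport group is φ = 0.25 × 0.5 / √(0.275 × 0.725) = 0.28.

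**4. Power of the planned t-test** (noncentral t, two-sided alpha 0.01, which the article applies to all tests):

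| Evaluable | Split | Detectable at 80% power | Power at 0.5 SD | Power at 0.3 SD |
|---|---|---|---|---|
| 171 | 47 vs 124 | 0.59 SD | 62% | 20% |
| 162 | 45 vs 117 | 0.61 SD | 59% | 19% |

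**5. What baseline adjustment could add.** Adjusting for baseline multiplies the residual variance by 1 − r² and the detectable difference by √(1 − r²), where r is the correlation between baseline and 24-month scores. The article does not give r; the values below are assumptions, with 171 evaluable and adjustment for baseline only.

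| r | Variance lower by | Detectable difference |
|---|---|---|
| 0.1 | 1% | 0.59 SD |
| 0.3 | 9% | 0.56 SD |
| 0.5 | 25% | 0.51 SD |
| 0.7 | 49% | 0.42 SD |

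**6. What adding sport group costs.** The variance inflation is 1/(1 − 0.28²) = 1.085, about 9%, which raises the detectable difference by √1.085, about 4%. With baseline and sport group together this gives 0.61 SD at r = 0.1 and 0.44 SD at r = 0.7, ignoring any outcome variance that sport group itself explains. Break-even with the plain t-test is at r² = 1 − 1/1.085 = 0.078, so r is about 0.28.

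**7. Symptomatic FAI.** The article gives no expected count. Assuming 10 to 20 cases among 162, the unadjusted detectable difference is 1.13 to 0.82 SD.

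**The case against.** Four points on the other side deserve weight.

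- *A reader might infer that the objective is change and that the t-test contradicts it.* The documents do not support that. The word appears in Study objectives only; the Abstract and Secondary outcomes describe a 2-year comparison, which is what the t-test performs. The defect is inconsistent wording, not departure from a settled estimand.
- *A reader might infer that ignoring baseline certainly wastes precision.* That is not established either. Eligibility admits only asymptomatic adolescents and excludes hip pain, trauma, surgery and paediatric hip disease. Baseline HOS may sit near its ceiling and predict little, and imbalance at entry should be limited. This is less persuasive for PedsQL, which is a generic measure. It does not touch confounding by sport group, sex or BMI.
- *A reader might infer that no calculation for the scores exists anywhere.* The abbreviations MID and SD are listed but not used in the text, so a fuller document may contain one. The criticism is confined to this article, which attributes the power to a calculation that covers incidence only.
- These are secondary, associational outcomes. The primary analysis and sample size are unaffected. The symptomatic-FAI counts are assumptions, and because that definition requires groin pain and reduced rotation, larger score differences are plausible. Thresholds of 0.8 to 1.1 SD are therefore not self-evidently inadequate.

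**Conclusion.** The point holds in two parts. The unadjusted t-tests leave a non-randomised contrast open to confounding that data already collected could reduce; at the planning rates sport group alone differs by 73% vs 41% between those with and without FAI. The Discussion's power claim for hip function and HRQL has no support in the article: the planned test detects about 0.6 SD at 80% power and has roughly 60% power at 0.5 SD.

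These figures assume the planning FAI rates, equal exposure groups and the stated attrition. The case for adjustment rests on confounding. The precision effect runs from a slight loss to a clear gain over the assumed r of 0.1 to 0.7 once sport group is included. The matter should be corrected, but it does not threaten the primary result.

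**What to change.** - In Secondary analyses, replace the t-tests with linear regression of the 24-month score on FAI status, baseline score, sex, BMI and sport group, and use the same model for symptomatic FAI.
- Make Study objectives agree with the Abstract, Secondary outcomes and Secondary analyses on whether the question concerns change or level at 2 years.
- In the Discussion, restrict the power claim to FAI incidence, or state the detectable score difference (about 0.6 SD unadjusted at two-sided alpha 0.01).

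No new data or participants are needed. The cost is revised text in the article and in any analysis plan, a variance increase of about 9% from including sport group, and a less favourable statement about power.

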#### Subgroup/sensitivity analyses

To assess whether the magnitude of the effect of sport activity on the development of FAI is significantly different in males than in females, we will add an interaction term between sex and sport specialist versus non-sport specialist to the primary logistic regression model. We hypothesize that sport specialization will be more strongly associated with incidence of FAI in males than in females.

No interim analyses are planned. All tests will be 2-sided with α = 0.01. We will use SAS 9.4 (Cary, NC) to perform all analyses.

